# An effectiveness-implementation hybrid trial of phone-based tobacco cessation interventions in the Lebanese primary healthcare system: protocol for project PHOENICS

**DOI:** 10.1186/s43058-023-00456-w

**Published:** 2023-06-26

**Keywords:** Tobacco cessation, Primary healthcare, Low-resource settings, Implementation

## Abstract

**Background:**

Tobacco use remains the leading cause of preventable disease, disability, and death in the world. Lebanon has an exceptionally high tobacco use burden. The World Health Organization endorses smoking cessation advice integrated into primary care settings as well as easily accessible and free phone-based counseling and low-cost pharmacotherapy as standard of practice for population-level tobacco dependence treatment. Although these interventions can increase access to tobacco treatment and are highly cost-effective compared with other interventions, their evidence base comes primarily from high-income countries, and they have rarely been evaluated in low- and middle-income countries. Recommended interventions are not integrated as a routine part of primary care in Lebanon, as in other low-resource settings. Addressing this evidence-to-practice gap requires research on multi-level interventions and contextual factors for implementing integrated, scalable, and sustainable cessation treatment within low-resource settings.

**Methods:**

The objective of this study is to evaluate the comparative effectiveness of promising multi-component interventions for implementing evidence-based tobacco treatment in primary healthcare centers within the Lebanese National Primary Healthcare Network. We will adapt and tailor an existing in-person smoking cessation program to deliver phone-based counseling to smokers in Lebanon. We will then conduct a three-arm group-randomized trial of 1500 patients across 24 clinics comparing (1) ask about tobacco use; advise to quit; assist with brief counseling (AAA) as standard care; (2) ask; advise; connect to phone-based counseling (AAC); and (3) AAC + nicotine replacement therapy (NRT). We will also evaluate the implementation process to measure factors that influence implementation. Our central hypothesis is that connecting patients to phone-based counseling with NRT is the most effective alternative. This study will be guided by the Exploration, Preparation, Implementation, Sustainment (EPIS) framework, supported by Proctor’s framework for implementation outcomes.

**Discussion:**

The project addresses the evidence-to-practice gap in the provision of tobacco dependence treatment within low-resource settings by developing and testing contextually tailored multi-level interventions while optimizing implementation success and sustainability. This research is significant for its potential to guide the large-scale adoption of cost-effective strategies for implementing tobacco dependence treatment in low-resource settings, thereby reducing tobacco-related morbidity and mortality.

**Trial registration:**

ClinicalTrials.gov, NCT05628389, Registered 16 November 2022.

**Supplementary Information:**

The online version contains supplementary material available at 10.1186/s43058-023-00456-w.

Contributions to the literature
This study will be among the first to evaluate primary care smoking cessation interventions in the Eastern Mediterranean.If the interventions are effective, they will inform broad dissemination to other Eastern Mediterranean countries and other low-resource settingsThis study is expected to generate unique evidence on the effectiveness and cost-effectiveness of population-based cessation interventions for waterpipe smokers.This study addresses an urgent need for research into implementation challenges that limit the impact of evidence-based interventions in low-resource settings to reduce the global burden of cancer.The expanded use of rigorous implementation science methods can be applied in other low-resource settings.

## Background

Tobacco use remains the leading cause of preventable disease, disability, and death globally due to its adverse health effects, including cancer, cardiovascular, and respiratory diseases [1, 2]. Although many regions of the world have made remarkable progress in curbing the tobacco epidemic, many low- and middle-income countries (LMICs) are lagging behind [3]. Among all World Health Organization (WHO) regions, the Eastern Mediterranean Region is making the least progress, where the number of smokers is projected to continue to increase by 2025 [3]. Lebanon, an Eastern Mediterranean country, has an exceptionally high tobacco use burden. Findings from a recent large nationally representative household survey in Lebanon indicated alarmingly high estimates of smoking prevalence: 35% of adults are current cigarette smokers, 39% are waterpipe smokers, and 4% are dual smokers [4]. Additionally, data from 2005 to 2015 collected from the National Cancer Registry of Lebanon revealed an increasing trend in lung cancer incidence, with the rate being the highest for females and the second highest for males in the Eastern Mediterranean Region [5]. Given the high burden of smoking in Lebanon, there is a persistent need to implement smoking cessation interventions.

The WHO Framework Convention on Tobacco Control (FCTC) is an international treaty that provides a framework for tobacco control measures to be implemented by its parties to continually and substantially reduce the prevalence of tobacco use and exposure to tobacco smoke [6, 7]. Article 14 of the FCTC addresses the issue of tobacco dependence treatment, defined as “the provision of behavioral support or medications, or both, to tobacco users, to help them stop their tobacco use” [8]. The following interventions have been identified as standard of practice for population-level tobacco dependence treatment: smoking cessation advice integrated into primary care settings, as well as easily-accessible and free phone-based counseling, and low-cost pharmacotherapy [8, 9]. There has been substantial progress in establishing strong scientific evidence supporting these interventions [8–10]. However, this evidence is mainly from high-income countries, and such interventions have been rarely evaluated in LMICs [11–13]. Guidelines for implementation of Article 14 recommend integrating tobacco cessation interventions into existing healthcare systems as an instrumental step towards comprehensive cessation support [8]. Although Lebanon ratified the WHO FCTC in 2005 [14], it has not prioritized implementing Article 14 and has been unable to integrate tobacco dependence treatment programs into its existing health system programs [14, 15]. This proposed project addresses the evidence-to-practice gap in the provision of tobacco dependence treatment within low-resource settings by developing and testing contextually tailored multi-level interventions while optimizing implementation success and sustainability.

As outlined in this protocol, the objective of Project PHOENICS (PHOne ENabled Implementation of Cessation Support) is to evaluate the comparative effectiveness of promising multi-component interventions for implementing evidence-based tobacco treatment in primary healthcare centers within the Lebanese Primary Healthcare Network.

More specifically, the aims of the study are to (1) adapt and tailor an existing in-person smoking cessation program to deliver phone-based counseling to smokers in Lebanon; (2) test the effectiveness and cost-effectiveness of a referral-based program that delivers smoking cessation services to primary healthcare patients; and (3) identify the multi-level determinants of implementation and sustainability using mixed methods.

## Methods/design

This protocol adheres to the Standards for Reporting Implementation Studies (StaRI) Statement (Additional file 1) [16].

### Regulatory approvals

This study was registered in ClinicalTrials.gov on November 16, 2022 (NCT05628389). The study was approved by the Institutional Review Board (IRB) at the American University of Beirut on June 3, 2022 (IRB#SBS-2022–0043) and the University of Florida on February 2, 2023 (IRB#202202537).

### Conceptual framework

The Exploration, Preparation, Implementation, Sustainment (EPIS) framework guides this study [17]. The EPIS framework describes four phases of implementation for evidence-based interventions, as well as domains and constructs that influence the implementation process and outcomes [17, 18]. In addition to defining the phases of implementation, EPIS will guide the formative assessment (Aim 1) to ensure intervention fit and alignment with multi-level factors, including patient characteristics, provider characteristics, inner context (i.e., primary healthcare centers), and outer context (i.e., health system) (Fig. 1). EPIS will also guide the implementation process and outcomes assessment (Aim 3). To complement EPIS, the measurement of implementation outcomes in Aim 3 will be guided by Proctor’s framework for implementation outcomes [19]. Application of EPIS will optimize the relevance of findings for generalizability and scalability, and integration of Proctor’s framework will allow for the evaluation of process-based measures of implementation in relation to implementation outcomes.

**Fig. 1 Fig1:**
[figure not shown]
Conceptual framework

### Study design overview

We propose an effectiveness-implementation hybrid (type 1) design [20] to test the comparative effectiveness of the multi-component interventions while gathering information on the multi-level factors that potentially inform the sustainment of the interventions in their setting (Fig. 2). First, we will adapt and tailor an existing in-person smoking cessation program at the American University of Beirut (AUB) Medical Center into an easily accessible phone-based counseling service for patients who smoke in Lebanon (Aim 1); we will collect pre-trial data using focus groups with patients who smoke, and we will also conduct a baseline assessment that includes surveys and in-depth interviews with providers from participating centers, and clinic workflow tailoring to further adapt the provider training and optimize the intervention fit to the primary healthcare center context. Then, we will conduct a group-randomized trial using three arms to compare the effectiveness and cost-effectiveness of the multi-component interventions (Aim 2): (1) ask about tobacco use; advise to quit; assist with brief counseling (AAA) as standard care; (2) ask; advise; connect to phone-based counseling (AAC); and (3) AAC + nicotine replacement therapy (NRT).

**Fig. 2 Fig2:**
[figure not shown]
Hybrid study design overview

Table 1 presents an overview of the multilevel intervention components by arm. The proposed multi-level intervention addresses barriers to tobacco treatment at the primary healthcare center and provider levels (e.g., lack of training, lack of systems to prompt tobacco treatment) and at the patient level (e.g., nicotine dependence, social norms). To address primary healthcare center- and provider-level barriers, we will implement clinic reminders and train providers and staff on best practices, including documentation of smoking status and referral to tobacco treatment. To address individual-level barriers, all patients will receive educational materials about the harms of smoking and the benefits of cessation, patients in Arms 2 and 3 will receive phone-based counseling, and patients in Arm 3 will receive phone-based counseling and NRT. We will then conduct follow-up surveys and in-depth interviews with providers and health system administrators to identify the multi-level barriers and facilitators to implementing and sustaining tobacco treatment interventions (Aim 3). Data from Aims 1 and 3 will allow us to assess the implementation context longitudinally. This design allows us to explore the clinical infrastructure and resources needed for effective implementation.

**Table 1 Tab1:** Multilevel intervention components by arm

Level	Motivating need/problem	Component	AAA	AAC	AAC + NRT
Clinic	Lack of integration into practice	Electronic reminders	◉	◉	◉
Provider	Insufficient knowledge, self-efficacy	Provider training	◉	◉	◉
Patient	Insufficient knowledge	Educational materials	◉	◉	◉
	Insufficient self-efficacy, motivation	Phone counseling		◉	◉
	Nicotine withdrawal symptoms	Nicotine patches			◉

*AAA* Ask, Advise, Assist, *AAC* Ask, Advise, Connect, *NRT* nicotine replacement therapy

### Hypotheses

Our central hypothesis is that connecting patients to phone-based counseling with NRT is the most effective alternative. We further hypothesize that (i) implementing AAA with providers will foster a supportive care climate for quit attempts, increase patient knowledge about the risks of smoking and the benefits of cessation, and modify social norms for tobacco use among smokers in Lebanon; (ii) connecting patients who smoke to phone-based behavioral counseling using AAC will increase the perceived benefits of cessation and improve norms, and promote self-efficacy among patients who smoke; and (iii) NRT will promote successful smoking abstinence by addressing nicotine withdrawal symptoms.

### Rationale for approach

Several considerations informed the selection of intervention components and targets. First, evidence on the effectiveness and cost-effectiveness of telephone counseling is not well-established in LMICs. Second, the incremental cost-effectiveness of NRT in conjunction with behavioral counseling has not been demonstrated in low-resource settings. Given the additional costs and limited access to NRT in LMICs, demonstrating the cost-effectiveness of NRT in LMICs is a critical question with implications for health system decision-makers. Third, we do not include an arm to test NRT without telephone counseling because of the evidence that behavioral support enhances the effectiveness of NRT [21, 22], and the fact that providing NRT as part of usual care in the primary healthcare center context would not be a feasible option. Finally, given the low prevalence of dual (cigarette/waterpipe) use in the recent national survey (5%) [4] and the relatively low participation of waterpipe smokers in the AUB Smoking Cessation Program (5%) [23], we anticipate that most participants will be exclusive cigarette smokers. However, we will include in our study waterpipe smokers, both exclusive and dual smokers, due to the high prevalence of waterpipe smoking in Lebanon (39%) [4], the need to identify effective interventions for waterpipe cessation, and the experience with waterpipe smokers in the AUB Smoking Cessation Program [23].

### Study setting

We will recruit 24 primary healthcare centers (each with > 500 unique patient visits annually) that are part of the National Primary Healthcare Network at The Ministry of Public Health (MoPH). The centers will be recruited from the Beirut metropolitan area, the largest in Lebanon, comprising one-third of its population, in order to optimize feasibility. Lebanon’s primary healthcare network comprises more than 250 primary healthcare centers distributed across the country and serving more than 50% of the population. The MoPH is the main authority that formulates and implements national health policies and programs. The participation of centers and providers will be coordinated through the Primary Healthcare Department at the MoPH.

### Approach for Aim 1

#### Focus groups

We will conduct eight focus groups with current tobacco users. Focus groups will follow a semi-structured guide with key questions to explore intervention adaptations informed by EPIS. Adult patients ($$\ge$$ 18 years) at primary healthcare centers who currently smoke cigarettes and/or waterpipe are eligible to participate in these focus groups.

#### Baseline provider surveys and in-depth interviews

We will conduct baseline surveys with all providers (physicians and nurses) in the 24 centers (*n* = 120, average 5 per center) to assess provider characteristics, provider attitudes, norms, and self-efficacy related to tobacco treatment, acceptability, and appropriateness of the proposed intervention components. In-depth interviews will be conducted with select healthcare professionals (*n* = *24*) to both explain and expand on the survey data. Survey findings will inform adaptations to the interview guide specific to the context of each center. The interviews will elicit attitudes towards and experiences in implementing tobacco treatment, potential barriers and facilitators to implementing tobacco treatment, and potential barriers and facilitators to implementing and sustaining the intervention. Interviews will be audio-recorded and transcribed verbatim.

#### Workflow tailoring

We will conduct workflow assessments via direct observation to optimize the integration of the intervention into the clinical workflow and further assess factors that may influence the adoption of the intervention. We will document current center policies, workflow, systems, and staff roles and responsibilities (in general and specifically related to tobacco treatment).

#### Pilot testing

We will pilot-test the intervention in one center. We will recruit 20 eligible patients into the most intensive intervention (AAC + NRT) to further test all components. We will follow the same procedures and methods described under Aim 2.

#### Convening and engaging the stakeholder advisory committee

We will convene an advisory committee to ensure that the research is aligned with key partners’ goals for developing an effective and sustainable model for tobacco dependence treatment in Lebanon. The committee will provide feedback at each phase of the study, offering local context for implementation and guiding dissemination activities and scaling-up of best practices in Lebanon and the region. The committee represents key partners who can serve as change agents in policymaking and clinical implementation. The committee will include the Director for Primary Healthcare and Social Health at the MoPH, two medical directors of primary healthcare centers, two nurses, and two patient advocates. The stakeholder advisory committee will be engaged in adapting and tailoring the intervention by providing feedback on the assessment tools and reviewing their findings to integrate themes and survey results into the final intervention to be tested in Aim 2.

#### Analysis

Descriptive statistics will be summarized for baseline measures overall and by arm. The pilot test with 20 patients will also be summarized in a descriptive manner. Qualitative data from the audio recordings of focus groups and interviews will be transcribed verbatim in Arabic and translated into English. The principal investigators’ and research staff’s fluency in Arabic and English will ensure conceptual equivalence [24]. The initial review of transcripts will follow a thematic content analysis approach given the structured nature of our inquiry into the specific domains surrounding the implementation context [25], using a framework method for rapid and multi-disciplinary assessment of key findings [26]. We will independently use a transcript summary template to abstract findings and generate a descriptive focus group-by-theme matrix for focus groups and center-by-theme matrix for interviews, developed with primary thematic categories based on the interview questions [27]. Review of completed matrices in team meetings will resolve discrepancies, establish inter-rater reliability, and inform the development of codebooks for in-depth analysis. The in-depth analysis of qualitative data will be conducted by trained coders using iterative stages of deductive and inductive coding, enabling identification and description of emerging themes [28]. Qualitative analyses of focus groups will include deductive codes to identify potential adaptations to intervention components and functions (e.g., counseling and referral practices). Qualitative analyses of interviews will involve within-center and cross-center analysis. Selective member checking will be conducted to enhance validity.

### Approach for Aim 2

#### Patient eligibility

Eligible patients will be adult ($$\ge$$ 18 years) patients from the participating centers who have visited the center in the past 6 months, are daily smokers ($$\ge$$ 5 cigarettes or $$\ge$$ 1 waterpipe session per day), are reachable by phone, are interested in quitting, live in Greater Beirut and are able to provide informed consent. We will include exclusive cigarette, exclusive waterpipe and dual cigarette/waterpipe smokers. We will exclude patients who are pregnant or nursing, patients for whom NRT is medically contraindicated and those enrolled in other tobacco treatment programs.

#### Recruitment and randomization

Permuted block randomization with will be used to randomize the centers. We will randomize at the center- rather than individual-level to test the effects of multi-level intervention components while preventing the threat of contamination within a center. We plan to enroll 1500 patients and estimate that we will be able to meet recruitment goals (average 75 patients per center in the AAC and AAC + NRT arms) within 9 months in each of the eligible centers. All participants will be offered remuneration at the 6-month assessment.

#### Sample size and power evaluation

Justification of the sample size is based on two-level hierarchical mixed-effects logistic regression. The analysis aims to compare the abstinence rate at 6 months post-intervention among the three intervention arms. In this design, the subjects are the level 1 units, and the centers are the level 2 units. All subjects in a particular center receive one of the possible interventions selected at random. Power is evaluated based on the differential effect size between the AAC + NRT and AAC arms, which is expected to be the smallest difference in the abstinence rate. Sample sizes of 480 in the AAC + NRT arm and 480 in the AAC arm, which are obtained by sampling 8 centers per arm with an average of 60 subjects per center, achieve 84% power to detect a difference in the abstinence proportions of 12%. The abstinence proportion at 6 months among AAC + NRT participants is assumed to be 32% under the alternative hypothesis, while the proportion among AAC participants is 20%. The test statistic used is the effect regression coefficient from a mixed-effects logistic regression model. The intra-cluster correlation coefficient is assumed to be 0.01 [29, 30], and the significance level of the test is 0.017 after Bonferroni adjustment. Considering the expected low abstinence rate in the AAA arm and a significant difference compared to both the AAC alone and AAC + NRT arms, and weighing ethical considerations to offer the more intensive intervention when possible, 240 subjects (an average of 30 subjects) per center from 8 centers will be necessary for the AAA arm to achieve more than 85% power with a 0.017 significance level. A total of 1,200 subjects will be necessary: 480 subjects (AAC + NRT; 60 subjects from 8 centers); 480 subjects (AAC; 60 subjects from 8 centers), and 240 subjects (AAA; 30 subjects from 8 centers). Considering a 20% drop-out rate, 1500 subjects will be enrolled.

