#### Analysis

All analyses in aim 2 will account for the multi-level nature of the group-randomized trial (i.e., patients nested within centers). Generalized linear mixed-effects models (GLMM) will form the basis of comparisons across intervention arms, including a random effect for the center. Models of binary outcomes (primary outcome and other cessation outcomes) will use a logit link to estimate relative risks to compare arms; models of continuous outcomes (e.g., quit attempts) will use an identity link assuming a Gaussian distribution, which will be verified to compare means. While balance across arms is expected, we will examine other covariates in the models as necessary, including sex as a biological variable. We will conduct pairwise comparisons to evaluate significant differences between arms, adjusting for multiple comparisons via the step-down Bonferroni method. The multi-level GLMM approach will also be used to evaluate the interventions’ causal direct and indirect effect estimates with mediator variables. Causal mediation analysis will be conducted to decompose the effects of mediators: total effect on the odds ratio scale = direct effect × indirect effect; total effect on the excess relative risk (ERR) scale = direct effect + indirect effect; and proportion mediated on the ERR scale = indirect effect/total effect × 100% using the counterfactual framework [38–42]. SAS CAUSALMED procedure will be used to estimate causal mediation effects. All causal models will include moderator variables. A sensitivity analysis will evaluate if the intervention effects differ by smoking type (cigarettes and waterpipe). The intra-cluster correlation coefficient will be estimated from the final model to inform future research.

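### The stated 84% power rests on a normal critical value; with 8 randomised centres per arm, a test on between-centre degrees of freedom has about 74–78% at the same inputs and alpha 0.017

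*Protocol article*

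**What the plan says.** The section Sample size and power evaluation (Protocol article, Aim 2) sizes the trial on AAC + NRT versus AAC, expected to be the smallest difference between arms. The inputs are all given:

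- Abstinence rates: "The abstinence proportion at 6 months among AAC + NRT participants is assumed to be 32% under the alternative hypothesis". For AAC the assumed rate is 20%.
- Size: "Sample sizes of 480 in the AAC + NRT arm and 480 in the AAC arm". The design behind these numbers is "sampling 8 centers per arm with an average of 60 subjects per center".
- Clustering: "The intra-cluster correlation coefficient is assumed to be 0.01".
- Alpha: "the significance level of the test is 0.017 after Bonferroni adjustment".
- Result: these numbers "achieve 84% power to detect a difference in the abstinence proportions of 12" percentage points.

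The test statistic is the arm coefficient of a mixed-effects logistic model. The Aim 2 Analysis section agrees: "Generalized linear mixed-effects models (GLMM) will form the basis of comparisons across intervention arms, including a random effect for the center". It adds pairwise comparisons with a step-down Bonferroni adjustment. Neither section names a reference distribution, degrees of freedom or a correction for a small number of centres.

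**The concern.** Centres are randomised, and every patient in a centre receives the same intervention. The arm effect is therefore a between-centre contrast, and its standard error depends on a between-centre variance estimated from 16 centres for the pair, or 24 for all three arms. With so few centres the uncertainty in that variance matters. A t reference on 14 or 21 df has clearly larger critical values than the normal, all the more at an alpha as small as 0.017.

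Two things are at stake. The first is whether the stated chance of detecting the planned difference is right for a test that holds its level. The second is conditional: if the analysis used the same normal reference as the power calculation, the pairwise test would exceed the alpha that the Bonferroni adjustment was meant to secure.

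**Working it through.** **Inputs** (all from Sample size and power evaluation): 32% and 20%; 8 centres × 60 = 480 per arm; ICC 0.01; alpha 0.017. Sidedness is not stated and is taken as two-sided, because one-sided gives 89–90%. The 20% drop-out does not enter: 480 is the number after drop-out (75 enrolled per centre × 0.8 = 60). The ICC is taken on the proportion scale.

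**Step 1: reproduce the 84%.**
- Design effect: 1 + (60 − 1) × 0.01 = 1.59.
- Variance sum: 0.32 × 0.68 + 0.20 × 0.80 = 0.2176 + 0.1600 = 0.3776.
- Standard error: √(0.3776 × 1.59 / 480) = 0.03537.
- Standardised effect: 0.12 / 0.03537 = 3.393.
- Normal critical value at two-sided 0.017: 2.387.
- Power: Φ(3.393 − 2.387) = Φ(1.006) = 84.3%.

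A pooled variance gives 83.7% and a log-odds-ratio version 82.9%. Ignoring clustering gives 96.9%. So the stated figure comes from a design-effect calculation with a normal critical value.

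**Step 2: same effect and standard error, between-centre df.** Power is the upper tail of a noncentral t with noncentrality 3.393.

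| Reference | Critical value | Power |
|---|---|---|
| Normal | 2.387 | 84.3% |
| t, 21 df (24 centres − 3 arms) | 2.592 | 78.0% |
| t, 14 df (16 centres − 2 arms) | 2.708 | 74.4% |

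The pooled and log-odds-ratio versions run about 1 to 2 points lower (77.1% and 76.5% on 21 df; 73.5% and 72.8% on 14 df).

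**Step 3: simulation check.** A centre-level t-test on beta-binomial data (200,000 trials) has 74.2% power on 14 df. Random-intercept logistic models fitted by maximum likelihood (two-arm and three-arm) give:

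| Reference for the model coefficient | Rejection under the null (nominal 1.7%) | Power |
|---|---|---|
| Normal | 3.3–3.4% | 85–86% |
| t, 21 df | 2.2–2.3% | 80–81% |
| t, 14 df | 1.7–1.9% | 77–78% |

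**Step 4: error rate if the normal were used.** In theory, the tail of a t distribution beyond ±2.387 is 2.6% on 21 df and 3.2% on 14 df. The maximum-likelihood simulation puts it at 3.3–3.4%. The overall range is 2.6–3.4% against 1.7%.

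**Step 5: effect of the planned step-down procedure.** Once a smaller p-value has been rejected, this contrast is tested at 0.05/2 or 0.05 instead of 0.05/3. The gain depends on the AAA rate, for which the protocol gives no figure. With centre-level t-tests on simulated beta-binomial trials:

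| Assumed AAA abstinence | Step-down power, AAC + NRT vs AAC |
|---|---|
| 8% | 87.7% |
| 10% | 86.6% |
| 12% | 85.0% |
| 15% | about 81% |
| 18% | about 79% |

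**Sensitivity to the ICC scale.** If 0.01 is read on the latent logit scale, the figures are 88.7% (normal), 83.2% (21 df) and 79.9% (14 df). None rounds to 84%, although the 21-df value comes close.

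**The case against.** The strongest reply has four parts.

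- **The 84% follows from its inputs.** This stands: there is no slip of arithmetic. The criticism is that a large-sample approximation was used where the number of randomised units is small.
- **The analysis is not tied to a z-test.** A reader might infer that the primary test has about twice its nominal error rate. The protocol does not support that. It names a model and a coefficient but no reference distribution, and the degrees-of-freedom method is commonly left to an analysis plan, which is not shown here. The error inflation is therefore conditional, and its size depends on the df and on the estimator. This does not rescue the stated power, however. If the analysis uses a t reference, 84% is too high for it. If it uses the normal, 84% belongs to a test that exceeds 0.017.
- **A valid test might reach 80%.** That figure comes from the mixed model with a 21-df reference, whose simulated error is 2.2–2.3%, so it does not quite hold 1.7%. It should not be quoted as the power of a level-holding test.
- **The trial has enough power anyway.** A reader might infer from 74–78% that the trial is undersized. The documents do not show this, because the planned step-down procedure recovers power at or above the stated figure when AAA abstinence is about 8–12%. But those rates are assumed, and the recovery is incomplete at 15%. The 84% is also stated at a fixed 0.017, so step-down does not make that statement correct.

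The missing numerical AAA rate is not itself an error: a condensed article may leave it to the full protocol.

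**Conclusion.** The point holds, at moderate severity. At the plan's own inputs and single-step alpha 0.017, power for AAC + NRT versus AAC is about 74% (14 df) to 78% (21 df), not 84%. A mixed-logistic simulation with a 14-df reference falls inside this range, at 77–78%. The shortfall is about 6 to 10 points: the chance of missing the planned difference is 22–26%, not 16%.

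This rests on a two-sided test, equal centre sizes and an ICC on the proportion scale, the reading that reproduces the stated figure. On the latent scale the 14-df and 21-df figures would be about 80% and 83%. Unequal centre sizes would lower all of them. No change in sample size follows from this point.

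**What to change.** In the Aim 2 Analysis section, specify small-sample inference for the arm contrasts. Options are between-within or Kenward-Roger type degrees of freedom, or a centre-level t-test or permutation test. For a pairwise contrast the conservative 14 df is preferable, because in the mixed-model simulation it stayed close to 0.017 while 21 df did not quite. If the analysis plan already does this, a cross-reference is enough.

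In Sample size and power evaluation, restate single-step power at 0.017 as about 74–78% and name the test it belongs to. If power under the step-down procedure is also reported, give it together with the AAA rate it assumes, for example about 85–88% at 8–12% and about 81% at 15%.

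The cost is a few sentences, one option in the model code and a less favourable headline power. No extra patients or centres are needed for this correction. The choice of reference should be fixed before outcome data are analysed by arm.
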